### Study intervention

#### Theoretical basis of the intervention

Telephone counselling will be based on Motivational Interviewing (MI) and cognitive behavioural skill building. MI is considered a client-centered, directive method to enhance intrinsic motivation for behavioural change by exploring and resolving ambivalence [19]. MI's primary goal is to trigger a decision and enhance commitment to this decision, for example by eliciting and selectively reinforcing change talk. MI's empathic, non-confrontational style may be particularly helpful in addressing smokers' ambivalence and defensiveness and in providing a safe counselling environment for smoking parents. When parents express a desire to quit smoking, telephone counselling will shift to cognitive-behavioural skill building. Smokers will be encouraged to create a supportive environment for quitting (e.g., arrange for smoking substitutes, avoid exposure to smoking cues). The overall approach to skill building is a problem-solving one. Smokers are encouraged to identify key barriers to quitting and to remaining quit (e.g., stress, urges and cravings, exposure to smoking cues, dysfunctional cognitions), to identify practical solutions, and to implement and evaluate these solutions. Cognitive-behavioural skill building will also incorporate relapse prevention strategies (e.g., anticipation of difficult situations/lapse to smoking). During telephone counseling, motivation to quit and self-efficacy to quit will be continuously monitored by counsellors. Counsellors will alternate MI and cognitive-behavioural skill building according to the participant's current need for motivation enhancement or skill enhancement.

#### Telephone counselling condition

In the telephone counselling condition, parents receive proactive telephone counselling based on MI and cognitive-behavioural skill building. Each participant receives up to seven counsellor-initiated phone calls across a period of approximately three months, respectively one 30-minute intake session and up to six additional 10-minute sessions. Telephone counselling will be conducted by professionals of STIVORO (Dutch expert centre for tobacco control). All counsellors are trained and experienced in the delivery of telephone counselling to support smoking cessation. Two different call schedules will be applied to participants who are willing to set a quit date and participants who are not willing to set a quit date.

##### Participants who are willing to set a quit date

Participants who are willing to set a quit date are offered 1-2 preparatory phone calls before undertaking a quit attempt. During the first phone call, participants are encouraged to set a quit date within 10-12 days. In the following, participants are offered up to six phone calls to support maintenance of smoking cessation. The phone calls focus on the following topics: reasons for smoking and reasons for quitting, nicotine dependence and nicotine withdrawal, craving, coping with difficult situations, weight gain and irritability, and relapse prevention. The first phone call (intake call) will take place approximately 10-12 days before the quit date; the second phone call will take place approximately three days after quit date; the third phone call approximately seven days after quit date; the fourth phone call approximately two weeks after quit date; the fifth phone call approximately four weeks after quit date; the sixth phone call approximately eight weeks after quit date; and the seventh phone call approximately twelve weeks after quit date.

##### Participants who are not willing to set a quit a date

Participants who are not willing to set a quit date will receive three phone calls. These phone calls are intended to increase the participant's motivation for smoking cessation by use of Motivational Interviewing. During these calls, counsellors aim to explore the participant's reasons for smoking and for quitting, to resolve ambivalence, and to enhance the participant's intrinsic motivation for behavioural change. Participants will receive the second phone call approximately three weeks after the first phone call (intake call). Approximately four weeks later the third phone will be made.

##### Supplementary brochures

All participants in the telephone counselling condition will receive three supplementary brochures on smoking cessation. All brochures are 4-page, colour-printed, A4-sized booklets which are designed specifically for the present study. The brochures have the following themes: 1) Deciding and preparing, 2) Undertaking a quit attempt, 3) Maintenance of smoking cessation. Each brochure includes additional information about smoking and smoking cessation, tips and exercises, and motivation or self-efficacy enhancing messages. Additionally, each brochure contains information which is relevant to parents (e.g., information about effects of second-hand smoke exposure for children). Participants will receive the first brochure immediately after start of the telephone counselling, the second brochure approximately 2-3 weeks after start of the telephone counselling, and the last brochure approximately 5-6 weeks after start of the telephone counseling.

#### Control condition

Participants in the control condition will receive a standard brochure (by STIVORO) on smoking cessation (Stoppen met roken: Willen en kunnen [Quitting smoking: Wanting to quit and being able to quit]). The brochure is a 40-page, colour-printed booklet (size: 12 × 16 centimeters). The brochure will be sent to participants randomized to the control condition within two weeks after baseline assessment. The brochure is divided into 5 parts: information about smoking and smoking cessation, reasons for quitting, tips and exercises, and maintenance of smoking cessation. At the end of the study, telephone counselling will be offered to all participants in the control condition.

### Data collection

An overview of the study design is presented in Figure 1. The baseline measurement will take place between January and July 2011. It is expected that the majority of the questionnaires will be administered digitally (the rest will be administered via mail). The post-measurement will take place approximately three months after start of the intervention. The follow-up assessment follows approximately twelve months after start of the intervention. At all three assessments, questionnaires will be filled in by both the parent and the child. Procedures will be identical across assessments.

**Figure 1 F1:**
[figure not shown]
**Study design**.

### Outcomes

In the proposed study, telephone counselling aims to increase cessation rates among smoking parents. The primary outcome measures will be: 1) sustained abstinence between post-measurement and follow-up measurement, 2) 7-day point prevalence abstinence at post-measurement (three months post-intervention) and follow-up measurement (twelve months post-intervention), and 3) 24-hours point prevalence abstinence at post-measurement and follow-up measurement. Additionally, biochemical validation of self-reported smoking cessation will be reported for a random sample (30%) of all study participants who report 7-day point prevalence at follow-up assessment, thereby allowing to estimate the occurrence of over-reporting of abstinence. Secondary outcome measures will include: a 50% reduction in the number of cigarettes smoked per day, occurrence of abstinence of at least 24 hours at some point during the study, implementation of smoking restrictions at home, increase in motivation to quit, use of and adherence to nicotine replacement therapy, number and duration of quit attempts, and change in smoking-related cognitions (e.g., attitudes towards smoking, self-efficacy, social norms). In addition, secondary outcomes will include smoking-related cognitions of children (e.g., attitudes towards smoking, self-efficacy, social norms, intention to smoke) and smoking behaviour of children.

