### Sample size calculation

Based on similar studies, we expected a 6% difference in 7-day point prevalence abstinence rates between the telephone counselling condition and the control condition at 12-months assessment (13% versus 7%, respectively). A statistical power of .80 was targeted. Hypotheses will be tested at a two-sided significance level of .05. The calculated sample size was corrected for participants who will be lost to attrition. Additionally, the sample size was corrected to allow for supplementary analyses of mediation and moderation.

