## Discussion

The present study protocol presents the design of a randomized controlled trial evaluating the effectiveness of proactive telephone counselling in smoking parents. The purpose of telephone counselling is to increase smoking cessation rates among parents. We hypothesize that cessation rates will be higher in the telephone counselling condition compared to the control condition, both at three-months post-measurement as well as twelve-months follow-up measurement. Additionally, we hypothesize that children of parents receiving telephone counselling will have more negative attitudes towards smoking, perceive stronger social norms against smoking, have higher self-efficacy to refrain from smoking, and have a lower intention to start smoking than will children of parents in the control condition.

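### Five abstinence results are named primary with none ranked first, while the sample size and the single .05 level fit only one of them

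*Protocol article*

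**What the plan says.** The Outcomes section of the protocol article reads "The primary outcome measures will be: 1) sustained abstinence between post-measurement and follow-up measurement, 2) 7-day point prevalence abstinence" at 3 and at 12 months, and then "3) 24-hours point prevalence abstinence at post-measurement and follow-up measurement". Written out, the primary results are:

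1. sustained abstinence from 3 to 12 months
2. 7-day abstinence at 3 months
3. 7-day abstinence at 12 months
4. 24-hour abstinence at 3 months
5. 24-hour abstinence at 12 months

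The abstract repeats the same set, so this is not a slip in one place.

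The sample size section uses one of the five: "we expected a 6% difference in 7-day point prevalence abstinence rates between the telephone counselling condition and the control condition at 12-months assessment", with 13% against 7%. It adds "A statistical power of .80 was targeted" and "Hypotheses will be tested at a two-sided significance level of .05". The Statistical analyses section names logistic regression for cessation rates and does not say which result decides. The Discussion expects higher cessation "both at three-months post-measurement as well as twelve-months follow-up measurement", but attaches no success rule to that expectation.

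**The concern.** Choosing the primary outcome is a decision that belongs in the protocol, and this article makes it: five results of equal standing. The sizing assumes something else, namely one outcome tested at the full .05. The two sections do not describe the same trial.

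At stake is what the .05 level protects. If any one of the five may carry the conclusion, .05 describes each test but not the claim. The five also differ in weight. A report of one smoke-free day at 3 months ranks equally with abstinence at 12 months. On the article's call schedule for parents who set a quit date, the intake call falls 10 to 12 days before that date and the seventh call about 12 weeks (84 days) after it. The last call is therefore about 94 to 96 days after intake, and the 3-month assessment may come before counselling has ended for some parents.

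**Working it through.** **1. The plan's own figure.** Inputs from the article: 13% v 7%, power .80, two-sided .05, 256 per arm. With mean rate 0.10:

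n per arm = [1.960·√(2·0.10·0.90) + 0.842·√(0.13·0.87 + 0.07·0.93)]² / 0.06² = (0.8315 + 0.3553)² / 0.0036 ≈ 392, or 784 in total.

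The stated 512 is not reproduced. Power at 256 per arm, before attrition, is Φ[(0.06·√256 − 0.8315)/0.4221] = Φ(0.304) = 62.0%. The shortfall is a separate matter; it is shown because it limits the remedies available here.

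**2. Independent tests.** Any direction: 1 − 0.95⁵ = 22.6%. Favouring counselling only: 1 − 0.975⁵ = 11.9%. The upper bound for any direction is 5 × .05 = 25%. The outcomes overlap by definition (seven smoke-free days include the last 24 hours), so independence overstates the error.

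**3. Overlapping outcomes.** I simulated null trials with 256 per arm, 40,000 per scenario, and two-proportion z tests standing in for logistic regression. Parents with 7-day abstinence also count as 24-hour abstinent, and sustained abstainers are a subset of those abstinent at both visits. All rates and overlaps are assumed. Each single test came out at 4.8% to 5.2%, as it should.

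| 7-day, 3 mo | 7-day, 12 mo | 7-day at both | Sustained | Extra with 24-hour only | ≥1 significant, any direction | ≥1 favouring counselling |
|---|---|---|---|---|---|---|
| 10% | 10% | 8% | 7.5% | 1 point | 11.5% | 5.7% |
| 10% | 10% | 6% | 5% | 1 point | 13.5% | 6.6% |
| 7% | 7% | 4.2% | 3.5% | 1 point | 14.0% | 7.1% |
| 10% | 10% | 6% | 5% | 2 points | 14.6% | 7.3% |
| 12% | 10% | 6% | 4% | 3 points | 15.9% | 7.9% |
| 10% | 10% | 3% | 2.5% | 2 points | 16.3% | 8.3% |

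A second model used 9% (7-day) and 12% (24-hour), a latent correlation between visits of 0.5 to 0.85, and sustained abstinence taken as 7-day abstinence at both visits. It gave 14.6% to 17.2% in any direction. With 24-hour abstinence closer to 7-day (10% and 11%), that model gave 12.5% to 14.9%. As a limiting case, an equal correlation of 0.9 among all five test statistics still leaves 10.1% in any direction and 5.1% favouring counselling.

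**4. Could the five be kept by adjusting?** Bonferroni over five gives .01 each. The article's rates then need [2.576·0.4243 + 0.3553]² / 0.0036 ≈ 583 per arm (1,166 in total) before attrition. At 256 per arm and .01, power is Φ[(0.96 − 1.0928)/0.4221] = 37.7%. The stated sizing therefore fits one primary outcome at .05 and not five.

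**The case against.** The strongest reply is that the inflation presupposes a rule the article never states. Nothing says that one success among five is enough, and the Discussion's expectation of benefit at both times can be read as asking for both. If all five had to be significant, there would be no inflation. This stands as a condition on the figures. It does not remove the point, because no joint rule is written either. A joint rule would also hold power at or below that of the weakest outcome, and the trial was not sized for that.

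A second reply is that a journal article condenses the full plan, and a multiplicity procedure is commonly left to the SAP, which is not shown. A reader might infer that all five will be tested with no control. The text does not support going that far: the .05 sentence sits in the sample size paragraph, and the analysis paragraph is silent on adjustment. The absence of a procedure is therefore not the fault raised here. The fault is the designation of five unranked primaries beside sizing for one, which the article itself makes.

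Third, a reader might infer that a false claim of effectiveness is about three times as likely as the stated .05. That mixes two rates. A false claim of effectiveness can only favour counselling, so about 5% to 8% must be set against 2.5%. Measured against .05, the simulated 5.7% to 8.3% is only about 1.1 to 1.7 times. The roughly two- to threefold ratio holds only when like is compared with like.

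Finally, sustained abstinence is listed first and could reasonably be preferred. It would be a legitimate single primary, but the article gives no rates from which to size it.

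**Conclusion.** The point holds as a mismatch within the article: five results share primary status, while the sample size and the undivided .05 level belong to one. If significance on any one is read as primary success, which the article neither states nor excludes, the chance of at least one false-positive primary result is roughly 11% to 17% in either direction against 5%, with 22.6% as the independent case. For errors favouring counselling it is about 5% to 8% against 2.5%. The count of five, the .05 level and the single sized outcome come from the text. The correlations, the 24-hour rates and the sustained rates do not, so the ranges show the order of magnitude and are not estimates for this trial.

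**What to change.** Before outcome data are seen, amend the Outcomes section and the abstract to name 7-day point prevalence abstinence at 12 months as the single primary outcome, tested at two-sided .05. This is the outcome already used for sizing. List sustained abstinence, 7-day abstinence at 3 months and both 24-hour results as secondary. If further confirmatory claims are wanted, a fixed testing sequence that starts with sustained abstinence after the primary is one option among several; otherwise report the four with confidence intervals and no confirmatory claim.

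The cost is wording in the protocol and matching wording in the SAP, and fewer outcomes can carry the headline claim. The fix neither lowers nor raises the power of the sized outcome. It does not cure the separate gap between 512 and the 784 that the stated inputs imply.

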### Statistical analyses

Analyses will be conducted to check whether the randomization has resulted in an equal baseline distribution of relevant participant characteristics across both conditions. In case of group differences at baseline, confounding variables will be included in subsequent analyses. To evaluate smoking cessation rates across groups, we will use logistic regression models. Effect sizes as well as confidence intervals will be reported. To evaluate smoking-related cognitions across groups (in both parents and children), analyses-of-variance and regression analyses will be used. Mediation and moderation will be tested in Mplus. In accordance with the intent-to-treat principle, all participants randomized to a condition will be included in analyses testing of the study hypotheses. In addition, a complete-case analysis will also be conducted, that is, only participants with outcome data on all assessments will be included in the analysis.

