### Randomization

Assignment to a group will be performed by a member of the research group who is not involved in the present study. Participants will be stratified by gender, educational level, and smoking intensity (as reported by participants in the baseline questionnaire). If partners who live in the same household participate in the study, randomization will be carried out at household level to avoid contamination between conditions.

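### Covariates are chosen on observed baseline differences, so the primary model is not fixed in advance and tends to omit the stratification factors; the cost is modest

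*Protocol article*

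**What the plan says.** The Protocol article, under Randomization, states: "Participants will be stratified by gender, educational level, and smoking intensity". The values come from the baseline questionnaire.

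Under Statistical analyses it plans a balance check: "Analyses will be conducted to check whether the randomization has resulted in an equal baseline distribution of relevant participant characteristics across both conditions". The consequence of that check is: "In case of group differences at baseline, confounding variables will be included in subsequent analyses". For the abstinence outcomes, "To evaluate smoking cessation rates across groups, we will use logistic regression models"; cognitions in parents and children are compared by analyses of variance and regression.

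This is the only covariate rule in the article. It names neither the characteristics to be checked nor what counts as a difference. No section says that the stratification factors are in the model, and none says that they are left out.

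**The concern.** If the randomisation is sound, a baseline difference between arms is a chance event and does not show that the variable matters for abstinence. Selecting covariates on such differences has three consequences.

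- **The model is unknown until data are seen.** The rule governs all later analyses, including five primary comparisons (sustained abstinence, and 7-day and 24-hour abstinence at two time points each). With no list and no criterion, the choice is open to judgement.
- **The effect measure is unknown too.** The odds ratio is non-collapsible: adding a prognostic covariate moves the target from the marginal to a conditional odds ratio, even under perfect balance.
- **The rule pulls against the design.** Factors balanced by stratification will seldom show a difference, so imbalance is a poor route into the model for the very variables judged important enough to stratify on.

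At stake are pre-specification of the primary result and a small amount of power.

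**Working it through.** **Inputs from the article.** Abstinence of "13% versus 7%, respectively" at 12 months; two-sided 5% level; target power 0.80; 256 parents per arm; three stratification factors.

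**Assumed, because the article does not give them.** The number of characteristics checked, a 5% criterion for a difference, 12 equal strata (2 × 3 × 2), permuted blocks of 4, the prognostic strengths, and no household clustering.

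**1. The plan's own figure and the base power.** Pooled formula per arm:

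[1.96·√(2·0.10·0.90) + 0.8416·√(0.13·0.87 + 0.07·0.93)]² / 0.06² = (0.8316 + 0.3553)² / 0.0036 ≈ 391.3, so 392.

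This does not reproduce 256 per arm. That is a separate matter; here it supplies only the base power with 256 per arm:

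Φ[(0.06 − 1.96·√(0.18/256)) / √(0.1782/256)] = Φ(0.304) ≈ 0.62.

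**2. How often chance would trigger the rule.** For k independent checks at 5%, the probability is 1 − 0.95^k:

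- k = 3: 14.3%
- k = 5: 22.6%
- k = 10: 40.1%
- k = 20: 64.2%

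These are illustrations only, since the article fixes neither k nor the 5%.

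**3. What the rule does with the stratification factors.** 3,000 trials of 512 parents were simulated per scenario. Log-odds effects are given in the order gender, education (per level), intensity. The null has 10% abstinence in both arms; the alternative has 13% against 7%. The rule was applied to the three factors only, so its columns show what happens when no other covariate is considered.

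| Assumed strength | Null rejection, rule | Null rejection, fixed adjustment | Power, rule | Power, fixed adjustment | Gain (points) | Mean odds ratio, rule | Mean odds ratio, fixed |
|---|---|---|---|---|---|---|---|
| Weak (0.3, 0.3, −0.6) | 4.2% | 4.5% | 63.6% | 64.2% | 0.6 | 2.02 | 2.05 |
| Moderate (0.5, 0.5, −1.0) | 3.5% | 4.0% | 61.7% | 63.4% | 1.7 | 2.01 | 2.08 |
| Strong (0.7, 0.7, −1.5) | 4.6% | 5.5% | 62.0% | 65.8% | 3.8 | 2.00 | 2.14 |

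No stratification factor reached p < .05 in any simulated trial, so the rule reproduced the unadjusted analysis every time. Simulation error per estimate is about 0.4 points for type I error and 0.9 points for power.

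A second simulation (8 strata, 4,000 trials), comparing unadjusted with fully adjusted models, gave power of 62.8% against 63.6% and, with stronger factors, 63.2% against 65.3%. The gains are 0.8 and 2.1 points.

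**4. The rule with other covariates in play.** Under simple randomisation with 10 independent covariates, 3 of them prognostic, and selection at p < .05 (4,000 trials), null rejection under the rule was 4.7% and 4.2%, against 4.6% with fixed adjustment. The power lost against fixed adjustment was 0.3 points with modest covariates and 3.7 with strong ones.

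**5. Which odds ratio.** The marginal odds ratio at the planning rates is (0.13 × 0.93)/(0.87 × 0.07) = 0.1209/0.0609 = 1.99. The rule's averages in the table stay near this value, while fixed adjustment moves to 2.05–2.14. The gap is small, but these are different quantities.

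**6. Can the model carry the factors?** Expected abstainers: 0.13 × 256 + 0.07 × 256 = 33.3 + 17.9 = 51.2. Condition plus three factors takes 4 or 5 parameters, giving 51.2/5 = 10.2 to 51.2/4 = 12.8 events per parameter. That is workable.

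**The case against.** The strongest reply is that the article does not refuse to adjust for the stratification factors. It only says what will be added in case of imbalance, and a fixed covariate list is commonly left to the statistical analysis plan. This stands as far as it goes: a reader might infer that the authors chose to leave the three factors out, and the text does not say so. But the point is not the missing list. The article positively states a selection rule that depends on the data, and a later plan with fixed covariates would have to override it.

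Second, a reader might infer that adjustment would be triggered by chance in 40% of such trials. The article gives no ten checks and no 5% criterion, and does not say that the check is a significance test. It also speaks of confounders, which normally requires a link with outcome as well. If only 3 of 10 variables qualify, the figure falls to 14.3%. The 40% is illustrative only.

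Third, a reader might infer a distorted test. Applied mechanically, the rule does not inflate the type I error. Nor is it established that standard errors are materially too wide. In a further simulation with 8 strata and blocks of 4, null rejection was 5.2% and 4.0% unadjusted against 5.5% and 4.6% adjusted, so the effect shows only with strong factors. In the table above, the adjusted test also falls below 5% in two scenarios.

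Fourth, balance on the three factors is likely but partly assumed. The article states no blocks or cut-points, nor how a couple randomised as one household is placed in a gender stratum. This stands, and for that reason the claim is that the rule tends to omit these factors.

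**Conclusion.** The point holds in a limited form. The article selects covariates on chance baseline differences, so the primary model and the odds ratio it estimates are not fixed in advance, and the rule tends to leave out the three factors used for stratification.

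The cost in power is about 1 to 2 points at 256 per arm, ranging from 0.6 to 3.8 over the prognostic strengths tried; the smaller gains are within simulation error. The type I error is not inflated. Scope for selective adjustment is a possibility that none of these figures measures. The sizes rest on the assumed strata, blocks, 5% criterion and prognostic strengths. The loss of pre-specification follows from the text alone.

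**What to change.** Replace the conditional sentence with:

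> All models comparing conditions (logistic models for abstinence, and the analyses of variance and regressions for parent and child cognitions) will include condition and the stratification factors gender, educational level and baseline smoking intensity, whatever the observed balance. Baseline characteristics will be described without significance tests, and no covariate will be chosen on baseline differences.

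The cognition models must be covered because the present rule reaches every later analysis. For the child outcomes, make clear that the factors are those of the parent. Add that the primary effect on abstinence is the covariate-adjusted (conditional) odds ratio, and show the unadjusted result as a sensitivity analysis.

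This is a free improvement. It changes wording only, since all three variables are already in the baseline questionnaire, and it needs no change to recruitment, sample size or follow-up.

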## Methods/Design

### Study Design

The present study is a 2-arm (telephone counselling versus control condition) randomized controlled trial with three assessments during a period of approximately one year. Participants will be 512 smoking parents and their 9-12 year old children. After giving informed consent and after completing the baseline assessment, 256 parents will be randomly assigned to the telephone counselling condition and 256 parents to the control condition. In the telephone counselling condition, parents will receive up to seven counsellor-initiated telephone calls and three supplementary brochures over a period of approximately three months. In the control condition, parents will receive a standard brochure on smoking cessation. Parent and child assessments will be identical across conditions and take place at baseline, three months after start of the intervention (post-measurement), and twelve months after start of the intervention (follow-up measurement). In both conditions, each parent-child couple will receive an incentive of 100 euro for their participation in all assessments.

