### Strengths and limitations

Strengths of the study include a 12-month follow-up assessment, which meets smoking cessation research recommendations [20]. A limitation of the study is that smoking cessation will be assessed by self-report. However, the present study counteracts reporting biases by informing participants that a random sample of participants will be asked for biochemical validation of self-reported smoking cessation. Biochemical validation of self-reported smoking cessation will be reported for a subsample (30%) of all study participants who report 7-day point prevalence at follow-up assessment, thereby allowing to correct for over-reporting of abstinence. Another potential limitation is that the impact of the intervention on children's cognitions about smoking may be limited by the degree to which their parents quit smoking.

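### Baseline adjustment of the cognition outcomes is tied to observed group differences; prespecified analysis of covariance on each baseline score would be more precise at no extra cost

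*Protocol article*

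**What the plan says.** Four statements in the protocol article bear on this.

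- **Method** (Statistical analyses): "To evaluate smoking-related cognitions across groups (in both parents and children), analyses-of-variance and regression analyses will be used". No baseline score is named as a model term, and none is excluded.
- **Covariate rule** (same section, following a check of baseline balance): "In case of group differences at baseline, confounding variables will be included in subsequent analyses". The cognition analyses come after this sentence and fall within its scope.
- **Outcome definitions** (Outcomes): among the secondary outcomes for parents is "change in smoking-related cognitions (e.g., attitudes towards smoking, self-efficacy, social norms". The child outcomes come in a separate sentence without the word change: "secondary outcomes will include smoking-related cognitions of children (e.g., attitudes towards smoking, self-efficacy, social norms, intention to smoke". The child hypotheses in Aim and hypotheses are likewise worded as differences in level between the arms.
- **Data available** (Data collection): "At all three assessments, questionnaires will be filled in by both the parent and the child". Baseline is one of the three assessments.

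Randomization stratifies by gender, educational level and smoking intensity, and keeps partners from one household in the same arm.

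**The concern.** In a randomised comparison, the main reason to adjust for an outcome's own baseline value is that it predicts the follow-up value. That reason holds whether or not the arms happen to differ at baseline. The stated rule uses the other criterion, observed imbalance, so the covariate set is settled only after the baseline data have been inspected, and a useful predictor stays out when the arms look alike.

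The consequence differs by outcome. For children, a level compared at follow-up with no baseline term leaves explainable variation in the residual. For parents, a change score does use baseline but forces its coefficient to be one, which costs precision unless the correlation is close to one.

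At stake is the precision of the comparison behind the trial's additional aim on children, and of a parent secondary outcome. The sample size was set for abstinence; no power or effect size is given for cognitions.

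**Working it through.** There is no figure for the cognition outcomes to reproduce. The check is how much residual variance each candidate analysis leaves.

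**Inputs**
- From Study Design: "256 parents will be randomly assigned to the telephone counselling condition and 256 parents to the control condition", taken as one child per parent with complete data.
- From Sample size calculation: two-sided 0.05 and power 0.80, borrowed from the abstinence outcome.
- Assumed: correlation r between baseline and follow-up score, 0.3 to 0.7, with equal variance at both times (set to 1).
- Assumed for illustration: an effect of 0.20 SD.

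**Residual variance per person**
- Follow-up score only: 1
- Change from baseline: 2 − 2r
- Adjusted for baseline: 1 − r²
- Adjusted relative to change: (1 − r²)/(2 − 2r) = (1 + r)/2

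| r | Adjusted, 1 − r² | Change, 2 − 2r | Adjusted/change | 256/(1 − r²) |
|---|---|---|---|---|
| 0.3 | 0.91 | 1.40 | 0.65 | 281 |
| 0.5 | 0.75 | 1.00 | 0.75 | 341 |
| 0.7 | 0.51 | 0.60 | 0.85 | 502 |

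**Children, against follow-up only.** The reduction is r²: 9%, 25% and 49%. The last column gives the arm size that an unadjusted comparison would need to match an adjusted one with 256.

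**Parents, against change.** The reduction is 1 − (1 + r)/2: 35%, 25% and 15%. The gain shrinks as r rises. Below r = 0.5 a change score has more variance than the follow-up score alone, because 2 − 2r then exceeds 1.

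**Power at 256 per arm for 0.20 SD**, from Φ(0.20 × √(256/2)/√v − 1.96), with v the residual variance:
- Follow-up only: 0.20 × 11.31 = 2.26; 2.26 − 1.96 = 0.30; power 62%.
- Adjusted: 66%, 74%, 89% at r = 0.3, 0.5, 0.7.
- Change: 48%, 62%, 83%.

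**Effect detectable with 80% power**, (1.96 + 0.84) × √(2/256) × √v: 0.248 SD follow-up only; 0.236, 0.214 and 0.177 SD adjusted.

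With an assumed 20% attrition (205 per arm) and r = 0.5, power for 0.20 SD is 53% follow-up only and 65% adjusted.

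These figures ignore household clustering and any further gain from the stratification factors.

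**The case against.** The best case for the plan is that analysis of variance and regression are families of methods. A repeated-measures analysis over the three assessments, or a regression containing the baseline score, satisfies the sentence. The imbalance rule speaks of confounders and does not bar an outcome's own baseline value. The article is condensed, and model terms for secondary outcomes usually belong in a fuller document.

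Much of this stands. A reader might infer that the plan discards baseline scores for parents and children alike. The documents do not support that: the parent outcome is change, which cannot be computed without baseline, and nothing excludes a baseline term for children. Silence about model terms would not, on its own, be worth raising.

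What does not fall away is the stated rule. The article says when baseline variables enter, and the trigger is observed difference rather than prognostic value. A fuller analysis plan that followed the article would inherit it.

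A reader might also infer that the expected child effect is small. The article concedes that "the impact of the intervention on children's cognitions about smoking may be limited by the degree to which their parents quit smoking", and its abstinence rates are "13% versus 7%, respectively". But the first gives no magnitude and the second concerns parents' quitting. No effect size or SD is stated for any cognition score, so the point does not rest on a small effect.

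**Conclusion.** The point holds as a minor one. The imbalance-triggered rule is a poor basis for choosing covariates, and on the plain reading it leaves child cognitions unadjusted for their own baseline in the usual case and parent cognitions analysed by a less efficient change score.

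The size depends on a correlation that the documents do not give, and on equal variances over time. The child figures apply only if follow-up scores would otherwise be compared alone; the parent figures apply only against a simple change score. If the intended models already contain the baseline score, the gain is zero and only the wording needs correcting.

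Leaving out a baseline covariate here costs precision and does not by itself bias the randomised comparison. The outcomes are secondary.

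**What to change.** For the cognition outcomes, replace the imbalance-triggered rule with one prespecified model. Regress each parent and child score at 3 months and at 12 months on condition, the same score at baseline, and gender, educational level and smoking intensity as used in stratification. Fit it whether or not the arms differ at baseline, and allow for household clustering where partners were randomised together. The clustering term follows from the randomisation unit and is not part of the precision gain above. The baseline balance check can remain as description, but should not select covariates for these models.

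The cost is a few sentences in the analysis plan, settled before outcome data are examined. No new data, visits or participants are needed. If a correlation turns out to be low, the extra covariate costs almost nothing at this sample size.
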